## Abstract

**Background:**

Injury, medical treatment, and rehabilitation can have major impacts on patients’ wellbeing. About 25-33% of the patients experience an acute stress disorder (ASD) or a posttraumatic stress disorder (PTSD) after injury. ASD is a relatively new diagnosis. Therefore, knowledge about patients’ experiences, the course of ASD and PTSD, and who is at risk for developing ASD or PTSD is lacking.

**Objective:**

The aims of this multi-method study are to explore patients’ experiences with injury (and their care) using a focus group study. Then, in the observational study, different courses of ASD, PTSD, and quality of life will be examined. In addition, this study will examine if these courses could be characterized by socio-demographic, clinical, and psychological variables. Consequently, a risk profile will be developed to determine which patients are at risk for developing ASD or PTSD during the 12 months after injury.

**Methods:**

Trauma patients treated in the shock room (in 2015) of the Elisabeth-TweeSteden Hospital will share their experiences with injury in the focus group study. Open, axial, and selective coding will be used to analyze the data. Concerning the observational study, patients treated in the shock room (during 2016 and 2017, Elisabeth-TweeSteden Hospital and Erasmus Medical Centre) will be asked to participate. The inclusion period is 12 months. Participants will complete the Impact of Event Scale-Revised, MINI-plus, the Hospital Anxiety and Depression Scale, and the World Health Organization Quality of Life-BREF after inclusion and at 3, 6, 9, and 12 months after injury. The NEO-Five Factor Inventory and the State-Trait Anxiety Inventory-Trait are completed after inclusion only. Repeated measures of latent class analysis and linear mixed models will be used to examine the research aims.

**Results:**

This project was funded in August 2015 by ZonMw. The results of the focus group study are expected in the first trimester of 2018. With regard to the observational study, recruitment is currently underway. Data collection will be completed in November 2018. The first results will be expected in the first trimester of 2019.

**Conclusions:**

This is the first multi-method study in trauma patients that examines patients’ experiences (qualitative design) as well as psychological disorders (observational prospective). This study will contribute to necessary information on psychological consequences after injury. Moreover, it provides knowledge about which patients to include in future psychological intervention research. Finally, awareness in clinicians about the psychological consequences can be created, so they are able to act more effectively to provide patient-oriented care.

**Trial Registration:**

Netherlands Trial Registry NTR6258; http://www.trialregister.nl/trialreg/admin/rctview.asp?TC=6258 (Archived by WebCite at http://www.webcitation.org/6xSCiO1bS)

## Introduction

Due to registration and implementation of specialized trauma care, the quality of medical treatment has been improved and survivorship has been increased [1-6]. Trauma is related to physical disabilities (eg, pain, fatigue and impaired wound healing), acute stress disorder (ASD), posttraumatic stress disorder (PTSD), and psychological distress [7-13]. Moreover, trauma patients experience an impaired quality of life (QOL) compared to the general population [14-20].

About 25% of trauma patients have subsyndromal ASD during hospitalization and about 30% had PTSD one month after injury [8,21]. Six months after injury, 49% showed a delayed onset of PTSD. This percentage decreased to 20% at 24 months after injury. A recent systematic review showed that patients diagnosed with ASD had a higher risk of developing PTSD [8]. However, the prevalence rate of patients with ASD who develop PTSD is unknown. Diagnostic criteria for ASD and PTSD are similar; however, dissociative symptoms (eg, depersonalization, derealization, and dissociative amnesia) are only emphasized in ASD and not in PTSD. Moreover, ASD can only be diagnosed within the first month after trauma and last for less than a month, while PTSD symptoms persist for at least one month after injury [22]. PTSD symptoms may begin either after trauma or months or years afterwards [23].

In addition to QOL, PTSD, anxiety, and depression are most frequently examined after injury [15-20]. However, information about ASD is scarce. The existing studies of ASD and PTSD are often cross-sectional. Moreover, in the case of an observational prospective design, examination of PTSD is limited to only several months after trauma. One or several measurements are needed to examine patients’ psychological recovery shortly after injury. Important information about the courses of ASD and PTSD (ie, main scores of onset and development, such as the stability of symptom severity over time) and patients’ characteristics is lacking [8,24,25]. More specifically, it is unknown if and in what way patients’ experiences with injury and treatment, for instance, in the shock room, contribute to psychological consequences. Moreover, factors related to communication between medical staff and patient, treatment of injury, and environment are not known. Gaining information about the development of ASD and PTSD and their sustaining risk factors will increase the quality of care because patients at risk can be offered psychological treatment, thereby preventing the development of psychological disorders, such as ASD and PTSD. Health care providers with the knowledge of medical and psychological consequences after trauma can better anticipate patients’ needs so that patient-centered care can be provided.

This multi-method study consists of a focus group study and an observational prospective study. The ultimate goal of this multi-method study is to provide valuable insight into the severity of psychological consequences, including ASD and PTSD, and the need for a psychological intervention study to prevent PTSD. First, focus groups are held to examine patients’ experiences with injury (and their care). In this way, potential factors related to the development of psychological problems (eg, depressive symptoms) and disorders (eg, anxiety, ASD, and PTSD) can be obtained and taken into account for the observational study (aim 1). Subsequently, an aim of the observational study is to examine the courses of ASD and PTSD (aim 2). In addition, it will be examined which socio-demographic (ie, sex, age, marital status, and education level), clinical (ie, type of trauma, Injury Severity Score (ISS), Glasgow Coma Score, being hospitalized, being treated on the intensive care unit, complications during treatment, and treatment by a medical psychologist or psychiatrist), and psychological variables (eg, anxiety, depressive symptoms, and personality) characterize the courses of ASD and PTSD. Subsequently, a risk profile will be developed to determine which patients are at risk for ASD and/or PTSD (aim 3). Finally, to study the effect(s) of the natural course of ASD symptoms on the development of PTSD, anxiety and depressive symptoms, and QOL across time will be analyzed (aim 4).

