### Inclusion and Exclusion Criteria

In order to be eligible to participate, patients (1) are treated in the shock room and (2) are aged 18 or older. Patients are excluded from participation in case of (1) severe traumatic brain injury (ie, Glasgow Coma Score ≤ 8), (2) dementia, or (3) insufficient knowledge of the Dutch language (verbal and writing). These criteria are used in the focus group and the study observational study.

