##### Additional Assessments

Socio-demographic information (ie, sex, age, marital status, and education level) will be obtained from patients at baseline. Clinical information, including date of trauma treatment, ISS, type of trauma mechanism (eg, traffic accident or fall), type of injury (eg, fracture), trauma treatment (eg, operation or medication), consult or treatment from medical psychology (yes/no and which type of treatment), hospital stay (yes/no), in case of hospital stay, admission to intensive care unit, and duration of hospital stay will be abstracted from the patients’ medical records. Possible logistic problems will also be recorded.

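### Psychiatric illness before the injury is not excluded, named for recording or adjusted for, so the aim 4 ASD effect is open to confounding and the risk profile can mix existing with new PTSD

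*Protocol article*

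**What the plan says.** **Purpose.** The abstract's Objective states that "a risk profile will be developed to determine which patients are at risk for developing ASD or PTSD during the 12 months after injury". Aim 4 (Introduction; Statistical Analysis, Observational Study; Table 2) uses linear mixed models for the effect of ASD on PTSD, anxiety, depressive symptoms and quality of life over time.

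**Who is left out.** Under Inclusion and Exclusion Criteria: "Patients are excluded from participation in case of (1) severe traumatic brain injury (ie, Glasgow Coma Score ≤ 8), (2) dementia, or (3) insufficient knowledge". The third item concerns Dutch. No psychiatric condition appears.

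**What is recorded.** The aim 3 clinical list in the Introduction runs "clinical (ie, type of trauma, Injury Severity Score (ISS), Glasgow Coma Score, being hospitalized, being treated on the intensive care unit, complications during treatment". Its remaining item, with the psychological variables that follow it, reads "and treatment by a medical psychologist or psychiatrist), and psychological variables (eg, anxiety, depressive symptoms, and personality) characterize the courses of ASD and PTSD". Under Additional Assessments, "Socio-demographic information (ie, sex, age, marital status, and education level) will be obtained from patients at baseline". The items taken from the medical record concern the injury, its treatment and the hospital stay, with one psychology item: "consult or treatment from medical psychology (yes/no and which type of treatment".

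**What is adjusted for.** The Statistical Analysis section names three covariates: ISS, type of injury and trauma mechanism. It gives psychological variables a mediating role.

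**When PTSD is measured.** Data Collection and Table 1 schedule PTSD, by MINI-Plus and IES-R, at baseline and at 3, 6, 9 and 12 months.

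**The concern.** Two questions depend on the patient's state before the injury.

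The first is aim 4. A disorder present before the injury plausibly makes ASD more likely. It plausibly also worsens later PTSD, anxiety and depressive symptoms and lowers quality of life. That makes it a common cause of exposure and outcome. If it is neither recorded nor adjusted for, its contribution is credited to ASD.

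The second is the risk profile. The aim is to find patients who will develop a disorder, so as to inform a later study on preventing PTSD. A patient who already had PTSD from an earlier event cannot have it prevented. If such patients sit in the same high-symptom course as new cases, the characteristics of that course describe both groups together. The profile also lacks a plausible marker that could be known on the day of injury.

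**Working it through.** **1. Is prior illness covered anywhere?**

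| Place in the protocol article | Content | Pre-injury psychiatric disorder? |
|---|---|---|
| Inclusion and Exclusion Criteria | Severe brain injury, dementia, insufficient Dutch | No |
| Introduction, aim 3 | Injury and care variables; psychologist or psychiatrist treatment | Only if the last item includes earlier treatment; timing not stated |
| Additional Assessments | Injury, treatment and stay; medical psychology consult or treatment | Not named; timing not stated |
| Statistical Analysis, covariates | ISS, type of injury, trauma mechanism | No |
| Personality (NEO-FFI, STAI-Trait) | Measured at baseline, after the injury | Partial proxy; as psychological variables, assigned to mediation |

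The closest stand-ins for earlier vulnerability are thus collected, but they are not planned as confounder adjustment in aim 4.

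**2. Can existing PTSD be told from new PTSD?** Partly. The Introduction says PTSD symptoms persist for at least one month after injury. A MINI-Plus result positive for PTSD within that month would therefore point to an earlier event. The Discussion has patients record when they completed the baseline questionnaire, so late baselines can be recognised. No passage says what is done with patients who are positive at baseline. The Discussion also expects some severely injured patients to complete baseline late, when a positive result no longer discriminates.

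**3. How large could this be?** The plan has no figure of its own to reproduce here, and its sample size of 300 does not enter. Everything below is an illustration.

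*Aim 4.* Bias = g × (p1 − p0), where g is the effect of prior illness on the outcome in SD, and p1 and p0 are its prevalence with and without ASD.

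- Set A assumes prior illness in 15–30% of patients, an odds ratio with ASD of 2–3, g of 0.4–0.6 SD, and ASD in 25%. Solve 0.25·p1 + 0.75·p0 = overall prevalence, with odds(p1) = OR × odds(p0).
  - 15%, OR 2: p1 = 0.223, p0 = 0.126. Bias = 0.4 × 0.097 = 0.039 SD.
  - 30%, OR 3: p1 = 0.484, p0 = 0.239. Bias = 0.6 × 0.246 (unrounded difference) = 0.148 SD.
- Set B assumes p1 of 20–40%, p0 of 10% and g of 0.5–0.8 SD.
  - Low end: 0.5 × 0.10 = 0.05 SD.
  - High end: 0.8 × 0.30 = 0.24 SD.

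The 25% is the Introduction's figure for subsyndromal ASD, so it is only a stand-in. If the effect size of 0.4 under Sample Size Calculation were a difference in SD units, Set A would be about 10% (0.039/0.4) to 37% (0.148/0.4) of it, and Set B 12.5% (0.05/0.4) to 60% (0.24/0.4). The article does not define that effect size, so the comparison may not be like with like.

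*Risk profile.* Let π be the share arriving with PTSD, all staying positive and none separated out, and i the true new PTSD among the rest. The existing share of apparent cases is π / [π + (1 − π)·i].

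- π = 2%, i = 30%: 0.02/0.314 = 6%.
- π = 5%, i = 20%: 0.05/0.240 = 21%.
- π = 10%, i = 10%: 0.10/0.190 = 53%.

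These shares fall if some earlier PTSD remits or if baseline positives are separated.

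**The case against.** The strongest objection is to a reading that a reader might infer: that patients with PTSD from an earlier event are counted as having developed it after this injury. The documents do not support that. PTSD is measured at baseline, the IES-R items refer to the injury, and nothing states that baseline positives count as new. A latent class analysis could show such patients as a course elevated from the start. Nor can one say that the MINI-Plus diagnosis is detached from this injury, because the criteria are in appendices that are not shown. The Introduction's remark that "PTSD symptoms may begin either after trauma or months or years afterwards" describes delayed onset and says nothing about how many patients arrive with PTSD. All of this stands, and it reduces the second half of the point to a missing separation rule.

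It can also be said that the variable lists are not exhaustive. The Introduction's list reads as closed, but the Statistical Analysis section gives its lists as examples and adds living situation. Treatment by a psychologist or psychiatrist might include earlier treatment. This stands too: absence from one list proves little. It does not answer the covariate statement, which names three variables, none psychiatric.

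Finally, the study is exploratory, and an article may leave abstraction fields and sensitivity analyses to a fuller document. That would excuse silence. Here the article itself states the covariates for an effect analysis and the role of the psychological variables, and those choices leave prior illness uncontrolled.

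**Conclusion.** The point holds in a limited form and is worth acting on before analysis. As written, the aim 4 effect of ASD is open to confounding by psychiatric illness that preceded the injury. Treating trait anxiety and personality as mediators does not cure this. The risk profile can mix existing with new PTSD because no stated rule separates patients positive on the MINI-Plus at baseline. It is not established that existing cases are counted as new, nor that the ASD effect is in fact biased.

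The size of either problem cannot be derived from the document. The illustrative ranges, 0.04 to 0.24 SD for aim 4 and 6% to 53% for the share of existing cases, rest on assumed prevalence, association, effect and persistence. They show only that a negligible effect should not be taken for granted.

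**What to change.** - **Additional Assessments:** abstract from the medical record, already opened for each patient, psychiatric diagnosis or treatment before the injury (yes/no) and PTSD before the injury (yes/no). Include patients already enrolled. State whether the existing psychology and psychiatry items refer to care before or after the injury.
- **Statistical Analysis, aim 4:** add pre-injury psychiatric history as a covariate in the mixed models.
- **Statistical Analysis, aim 3:** add it as a candidate characteristic of the courses.
- **Sensitivity analysis:** repeat the PTSD courses and the risk profile without patients who have recorded pre-injury PTSD, or a positive MINI-Plus PTSD result at a baseline completed within one month of injury. For later baselines, rely on the record alone.

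The cost is two abstraction fields, one covariate and one repeated analysis. The downside is small: records under-capture psychiatric history, so some confounding will remain and should be acknowledged.

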## Methods

### Design

First, using a qualitative focus group study design, patients’ perspectives on the injury, treatment in the shock room and hospital, and rehabilitation are explored. A focus group is a commonly used method of qualitative research as it is a valid and reliable technique. Moreover, focus groups facilitate the in-depth exploration of a person’s perspective through group interaction. Participants can be triggered by a comment from another participant [26,27], and by the concept of sharing and comparing [28]. Then, as an extension of the focus group study, the observational prospective cohort study will examine ASD, PTSD, anxiety and depressive symptoms, and QOL. This will be assessed up to one year after treatment for physical trauma. A flow diagram of the observational study design and the main procedures that patients will undergo during the course of the observational study are shown in Figure 1.

### Participants and Centers of Recruitment

Trauma patients treated in the shock room in 2015 of the Elisabeth-TweeSteden Hospital are asked to participate in the focus group study. A shock room is situated at the Emergency Department and is reserved for physical trauma patients (ie, all types of injury) with a potentially life-threatening situation.

**Figure 1 figure1:**
[figure not shown]
Flowchart of the study design. ASD: acute stress disorder; IC: informed consent; PTSD: Posttraumatic stress disorder; QOL: quality of life.

Concerning the observational study, all adult patients who have been in the shock room at the Emergency Departments of the Elisabeth-TweeSteden Hospital (Tilburg) or the Erasmus Medical Centre (Rotterdam, The Netherlands) are asked to participate. The inclusion period is about 12 months after the start in November 2016.

### Sample Size Calculation

This project is exploratory in nature. Moreover, the focus is on examining the stability of results. The sample size was calculated only for the observational study. According to the Dutch trauma registry, the shock room admission was about N=1440 in 2013 and N=986 in 2016 in the Elisabeth-TweeSteden Hospital. Using a mean of these admission numbers of (N=1213, alpha=0.05, beta=0.80, and effect size=0.4), it was estimated that N=300 would be sufficient. This was also based on Monte Carlo simulations [29].

### Inclusion and Exclusion Criteria

In order to be eligible to participate, patients (1) are treated in the shock room and (2) are aged 18 or older. Patients are excluded from participation in case of (1) severe traumatic brain injury (ie, Glasgow Coma Score ≤ 8), (2) dementia, or (3) insufficient knowledge of the Dutch language (verbal and writing). These criteria are used in the focus group and the study observational study.

### Study Procedures

#### Focus Groups

Trauma patients who were treated in the shock room of the Elisabeth-TweeSteden Hospital during 2015 were asked to participate in a qualitative focus group study. Patients were divided into 3 groups: (1) patients who went home after treatment in shock room (no hospitalization) or, in case of hospitalization, they had an ISS of less than 16; (2) ISS equal or higher than 16, and (3) mild or moderate traumatic brain injury (Glasgow Come Score > 8). Six to 10 patients were invited to participate in each group. To obtain a representative sample of the trauma population, the division into groups was based on type of injury, sex, and age. The purposive sampling method was used [26,27].

The focus group meetings took place in a conference room at the Elisabeth-TweeSteden Hospital. Each focus group was guided by a moderator and an assistant. The patients were asked to share their experiences by answering the main question, “What experience related to your injury impressed you the most?” Their experiences were clustered on a flipchart on the basis of the trauma procedure: (1) moment of injury, (2) treatment in the ambulance or the trauma helicopter, (3) treatment in the shock room, (4) hospital stay, (5) moment of discharge, and (6) period after discharge and/or rehabilitation. Finally, another main question, “In what way did you need and received psychological treatment?”, was discussed. At the end of each focus group, participants were asked to complete questions about their socio-demographic status (ie, age, sex, marital status, and education level). In addition, they completed the Impact of Event Scale revised (IES-R) for PTSD and the Hospital Anxiety and Depression Scale (HADS) for anxiety and depressive symptoms. All focus groups had the same structure and were audio-recorded. The duration of the meeting was about 90 minutes.

#### Observational Study

The emergency doctor or the resident will ask patients to participate in this study as soon as they can talk and are lucid. If the emergency doctor or the resident is not able to ask the patient to participate (eg, due to transferring the patient to another department in the hospital), the researcher will ask the patient as soon as possible to participate in this study. The researcher will check medical records to see whether there are patients that have not yet been asked to participate in the study.

Patients will sign two informed consents. First, in the emergency department (after being treated in the shock room and being informed by the doctor). Then 1-5 days later, the patient will be asked to confirm participation again to make sure that they have sufficient time to consider participation in the study. In the case of a patient who is unconscious, the patient will be informed by the researcher and asked to participate as soon as the patient is lucid. If a patient declines participation by not signing the second informed consent, all obtained information will be destroyed.

After confirming participation, the patient will complete a questionnaire on socio-demographic questions, ASD and PTSD, anxiety and depressive symptoms, personality, and QOL at the first time-point (ie, baseline). Clinical information will be retrieved from patients’ medical records. The measurement points are at inclusion, 3, 6, 9, and 12 months after injury (see Figure 1). 

